## Results

This study was approved by the university IRB on March 10, 2021, and initiated on May 1, 2021. Recruitment started on June 22, 2022, and the first participant was enrolled on June 15, 2022. The trial is expected to be completed in September 2023.

## Discussion

### Principal Findings

This paper has presented the background and design for a SMART-HEALTH study investigating the feasibility of a home-based M2M exercise program, using an adaptive design for adults with SCI. Exercise is a critical health-enhancing behavior; yet, substantial evidence supports various challenges of engaging in the recommended physical activity levels for many people with SCI. Tele-exercise programs may be suitable to overcome logistic barriers to exercise participation (eg, lack of transportation, travel time, and accessible facilities) and potentially more cost-efficient and convenient than programs offered in the community [16]. In addition, the application of the adaptive design to exercise intervention allows investigators to provide more tailored and targeted program delivery for people with SCI based on their needs while maintaining systematic approaches and scientific rigor. The ultimate goal of the SMART-HEALTH study is to find effective strategies to help guide and shape the exercise behavior of people with SCI toward higher levels of adoption and sustainable exercise participation. The SMART-HEALTH study will test multiple sets of adaptive intervention designs and their delivery strategies to optimize future intervention.

### Strength and Limitations

The trial uses an innovative study design to address adherence to exercise interventions among people with SCI. It addresses a growing need among physicians treating patients with mobility disabilities to have easily accessible eHealth home-based exercise videos that can be tailored to the functional level of their patients. This is a pilot trial to assess the feasibility of using a SMART design and is not powered for effectiveness.

### Conclusions

The trial serves to inform the development of adaptive interventions, including whether, how, or when to alter treatment intensity, type, or delivery. In addition, this can determine the actual efficacy of home-based exercise based on the SCI-specific physical activity programs for improving adherence to the program and physical activity.

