**Objective:**

The primary aim of this study is to test the feasibility of a tele-exercise program that applies an adaptive intervention design for 30 adults with SCI, targeting increases in adherence to the exercise program and physical activity participation.

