**Methods:**

The Sequential Multiple Assignment Randomized Trial for Home-based Exercise and Lifestyle Tele-Health (SMART-HEALTH) is a 12-week, home-based, movement-to-music (M2M) program. The goal of a SMART-designed study is to develop an adaptive intervention that modifies support provisions based on response levels. In SMART-HEALTH, 2 groups of participants will undergo 3-week and 6-week asynchronous M2M interventions in the first phase. Participants who did not achieve the desired adherence rate (≥95% of video watch minutes) will be rerandomized into M2M Live (switch) or individualized behavioral coaching (augmented with the asynchronous M2M program). The study will primarily assess rates of recruitment or enrollment, adherence and retention, timing to identify nonresponders, and scientific outcomes (eg, physical activity and exercise self-efficacy). The study will qualitatively evaluate the acceptability of the study using semistructured interviews among participants who complete the 12-week intervention.

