We propose a pilot, 2-phase SMART examining the feasibility of a 12-week tele-exercise intervention for improving adherence to the program and physical activity behavior in 30 adults with SCI, named the Sequential Multiple Assignment Randomized Trial for Home-based Exercise And Lifestyle Tele-Health (SMART-HEALTH). The applied exercise intervention is a novel movement-to-music (M2M) video program that incorporates enjoyable movement routines accompanied by music to improve cardiovascular capacity, muscular strength and endurance, balance, and range of motion. Evidence supports the efficacy of M2M in enhancing functional mobility (the timed up and go and 6-minute walk test) among adults with multiple sclerosis [35]. Also, 1 ongoing tele-exercise trial is testing the effectiveness of the M2M video program that includes >400 adults with physical disabilities (NCT03024320) [36]. The modified and scaled-up M2M program was delivered at a state-of-the-art exercise facility for people with disabilities (Lakeshore Foundation). This program integrates the principles of SCT through weekly newsletters that contained educational information aligned with the key constructs of SCT (self-efficacy, outcome expectation, knowledge, self-regulatory strategies, facilitators, or barriers) for promoting and maintaining behavior change.

The primary aim of this study is to assess the feasibility of the 12-week tele-exercise intervention with the SMART design application. The assessment of the feasibility focuses on recruitment or enrollment, adherence, and retention rates, resources and management issues, timing to identify nonresponders, and adverse events (AEs). The secondary aim is to qualitatively assess the acceptability of the SMART-HEALTH intervention. Acceptability will be assessed qualitatively via thematic analysis of semistructured exit interviews conducted at 3 months from baseline, with participants who complete the pilot study. The tertiary aim is to estimate average intervention effects and variability on the scientific outcomes (eg, video watch minutes, self-reported vs objectively measured physical activity) to determine effect sizes and potential for a larger trial. The information yielded by such a feasibility study will be critical for designing larger-scale projects that can establish the actual efficacy and effectiveness of the future SMART-HEALTH study.

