#### Prerecorded, Asynchronous M2M Videos

Both groups of participants receive the same exercise prescriptions at the first phase of the intervention. The M2M program provides a sequence of exercise routine, which is accompanied by music to improve range of motion, muscular strength and endurance, cardiovascular capacity, and balance or proprioception. The weekly exercise video is set to progressively increase the exercise minutes to enable the participants to reach and exceed the recently published SCI exercise guideline [38]. Both groups of participants will begin with 30 minutes of exercise (twice weekly or 15 minutes per session) and increase the minutes incrementally until they reach the SCI guideline of 90 minutes at week 6 (3 times weekly or 30 minutes per session) and 150 minutes at week 9 (3 times weekly or 50 minutes per session). The detailed exercise prescription is presented in Table 1.

**Table 1 table1:** Description of exercise components and prescriptions in minutes per week.

Exercise Component	Week 1, minutes	Week 2, minutes	Week 3, minutes	Week 4, minutes	Week 5, minutes	Week 6, minutes	Week 7, minutes	Week 8, minutes	Week 9, minutes	Week 10, minutes	Week 11, minutes	Week 12, minutes
ROM I^a^	5	5	5	5	5	N/A^b^	N/A	N/A	N/A	N/A	N/A	N/A
ROM II	N/A	N/A	N/A	5	5	5	5	5	5	5	5	5
Muscular Strength I	5	5	5	5	N/A	N/A	N/A	N/A	N/A	N/A	N/A	N/A
Muscular Strength II	N/A	N/A	N/A	N/A	5	5	5	5	N/A	N/A	N/A	N/A
Muscular Strength III	N/A	N/A	N/A	N/A	N/A	N/A	N/A	N/A	5	5	5	5
Aerobic I	N/A	N/A	N/A	5	5	N/A	N/A	N/A	N/A	N/A	N/A	N/A
Aerobic II	N/A	N/A	N/A	N/A	N/A	10	10	10	10	10	10	10
Aerobic III	N/A	N/A	N/A	N/A	N/A	N/A	N/A	N/A	10	10	10	10
Aerobic IV	N/A	N/A	N/A	N/A	N/A	N/A	N/A	10	10	10	10	10
FSB I^c,d^	5	5	5	5	N/A	N/A	N/A	N/A	N/A	N/A	N/A	N/A
FSB II^c,d^	N/A	N/A	N/A	N/A	5	5	5	5	N/A	N/A	N/A	N/A
FSB III^c,d^	N/A	N/A	N/A	N/A	N/A	N/A	N/A	N/A	5	5	5	5
Cooldown	N/A	5	5	5	5	5	5	5	5	5	5	5
Total exercise per session	15	20	20	30	30	30	30	40	50	50	50	50
Total exercise per week	30	40	40	60	60	90	90	120	150	150	150	150

^a^ROM: range of motion.

^b^N/A: not available.

^c^FSB: functional strength and balance.

^d^Participants will be instructed to repeat the prerecorded videos 2 times per week for the first 5 weeks (week 1-5) and then increase the repetition to 3 times per week for the second 7 weeks (weeks 6-12).

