### Analysis

#### Overview

All data will be exported and analyzed using SPSS (version 22.0; IBM). Data will be initially examined for variations, outliers, errors, and patterns of missing values. Missing data will be inputted using multiple imputation techniques where necessary based on the assumption that the missingness mechanism is at random. All statistical analyses will be conducted in an intent-to-treat manner at the individual level.

#### Aim 1

The primary outcomes of this pilot study will include enrollment rate, retention rate, and completion rate of surveys and physiological measures. Process, resource, and management feasibility will initially be examined via percentage, frequency analysis, and descriptive statistics.

#### Aim 2

A qualitative study of participants’ experiences, perceptions, and suggestions regarding the SMART-HEALTH program will be completed at week 12. This study will refine the study components and implementation processes for a future trial. In brief, participants who complete the SMART-HEALTH program will take part in single, one-on-one semistructured interviews with questions focusing on what worked and did not work. Interviews will be audio-recorded, transcribed, and analyzed using thematic analysis using a qualitative descriptive design [43].

#### Aim 3

The study will estimate recruitment and retention rates, as well as estimate outcomes and variability of efficacy outcomes for a larger clinical trial (aim 3), which will measure rates of physical activity, psychosocial variables (eg, depression), and physiological variables (eg, lung function). Additional fidelity measures will include adherence to exercise intervention (minutes of sessions viewed), number of coaching sessions completed, and intervention safety (number of AEs).

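### The Conclusions credit this pilot with determining the efficacy of home-based exercise, and the Abstract puts scientific outcomes among what is primarily assessed; both conflict with the feasibility aims stated elsewhere

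*Protocol article*

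**What the plan says.** On what the trial can conclude:

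- Conclusions: after saying that the trial informs the development of adaptive interventions, the text adds that "this can determine the actual efficacy of home-based exercise based on the SCI-specific physical activity programs". The end of that sentence applies the claim to adherence and physical activity.
- Strength and Limitations, immediately before: "This is a pilot trial to assess the feasibility of using a SMART design and is not powered for effectiveness".
- Introduction, last paragraph: efficacy and effectiveness are left to larger-scale projects that this pilot would help to design.

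On the rank of the outcomes:

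- Abstract, Objective: "The primary aim of this study is to test the feasibility of a tele-exercise program".
- Abstract, Methods: the items the study will primarily assess are recruitment, adherence and retention rates, then "timing to identify nonresponders, and scientific outcomes (eg, physical activity and exercise self-efficacy".
- Introduction, aims: "The tertiary aim is to estimate average intervention effects and variability on the scientific outcomes".
- Analysis, Aim 1: "The primary outcomes of this pilot study will include enrollment rate, retention rate, and completion rate of surveys and physiological measures".

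On the design: "Both groups of participants receive the same exercise prescriptions at the first phase of the intervention" (Prerecorded, Asynchronous M2M Videos). Study Design has response checked at week 3 in group 1 and week 6 in group 2. Nonresponders are rerandomised to M2M Live or to asynchronous M2M with behavioural coaching, and responders continue asynchronous M2M.

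**The concern.** An efficacy conclusion needs a contrast that isolates the treatment and enough precision to read it. The article states that the second is absent, and the design does not supply the first for exercise itself. The Conclusions nevertheless promise the result.

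The Abstract adds to the problem. If scientific outcomes count as primarily assessed, a change in physical activity over 12 weeks could be presented as a leading result of the trial, although the aims rank it third. The Abstract and the Conclusions are the parts most readers see, so an overstatement there carries more weight than the accurate statements in the body.

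**Working it through.** **1. The plan's own figure.** Power gives a sample size of 30, attrition of 25% and an enrolment target of at least 40.

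30 / (1 − 0.25) = 40, which reproduces the target.

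The basis given is guidance for pilot trials. No alpha, power, effect size or SD is stated, so there is no power calculation to reproduce and nothing in the sample size that would support an efficacy conclusion.

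**2. The claims side by side.**

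| Place | What the trial delivers |
|---|---|
| Conclusions | Efficacy of home-based exercise can be determined |
| Strength and Limitations | Feasibility; no power for effectiveness |
| Introduction | Feasibility first; efficacy and effectiveness left to larger projects |

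The change of word from effectiveness to efficacy does not reconcile the first two rows, because the Introduction defers both.

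**3. What the randomisations compare.**

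| Step | Options | Exercise in each? |
|---|---|---|
| First randomisation | Asynchronous M2M, response check at week 3 or at week 6 | Yes, same prescription |
| Second randomisation (nonresponders) | M2M Live, or asynchronous M2M plus coaching | Yes |
| Responders | Continue asynchronous M2M | Yes |

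No arm is without M2M. The effect of exercise itself on physical activity can therefore be read only from uncontrolled pre-post change. The randomised comparisons concern when to check response and what to offer nonresponders.

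**4. Precision of those comparisons (illustration).** Inputs: 15 per group from 30 randomised 1:1 (Study Design), and 5 per group as the smallest expected rerandomised group (Power). Assumptions that are mine: a continuous outcome, equal variances, no baseline adjustment, and a two-sided 95% interval.

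Half-width in SD units = t(0.975, 2n − 2) × √(2/n)

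- n = 15: 2.048 × √(2/15) = 2.048 × 0.365 = 0.75 SD
- n = 5: 2.306 × √(2/5) = 2.306 × 0.632 = 1.46 SD

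For range, 10 vs 10 gives 2.101 × 0.447 = 0.94 SD. Analysing all 40 enrolled as 20 vs 20 gives 2.024 × 0.316 = 0.64 SD.

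**5. Rank of scientific outcomes.**

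| Place | Rank |
|---|---|
| Abstract, Methods | Among the items primarily assessed |
| Abstract, Objective | Primary aim is feasibility |
| Introduction | Tertiary aim |
| Analysis, Aim 1 | Not among the primary outcomes named |

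The first row cannot be squared with the third.

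**The case against.** The best defence is that the hierarchy is clear to anyone who reads the whole article. Feasibility is the primary aim in two places, the only sentence that uses the term primary outcomes names no scientific outcome, and the limits on power are stated one section before the disputed sentence. The Abstract's adverb may only contrast quantitative assessment with the qualitative interviews in its next sentence. This limits how serious the point is. It does not remove it, because the Conclusions still state something that the Introduction and the limitations deny.

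Several stronger readings are tempting, and the document does not support them:

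- *The lack of a non-exercise arm is a design defect.* It is not one for a feasibility SMART, which is meant to compare decision points and second-stage options. It only rules out a conclusion about exercise itself.
- *Nothing about efficacy can be estimated at any sample size.* This is too broad. Adherence is the share of prescribed video minutes watched, and differences in it between randomised options are estimable in principle.
- *The second randomisation varies only the support given.* M2M Live also changes delivery and content: it is one-on-one and synchronous, with customised movements and music.
- *Adherence is assigned inconsistently.* It appears under feasibility and again under Aim 3, but one measure can serve two aims.
- *The pilot's effect estimate will set the size of the next trial.* The tertiary aim does say "to determine effect sizes and potential for a larger trial", but the same sentence is about estimating effects and variability. Nowhere does the article say that the pilot's point estimate will be the later target difference.

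It is also fair to say that the interval widths in the working only restate that the groups are small, which the article concedes. They illustrate the gap between the claim and the design; the contradiction does not depend on them.

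**Conclusion.** The concern holds as a matter of wording and interpretation. The Conclusions claim a property that the design lacks and that two other sections disclaim. The Abstract's list of what is primarily assessed conflicts with the tertiary rank given to scientific outcomes in the Introduction and with the primary outcomes named under Analysis, Aim 1.

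For scale, a between-group difference would be known to within about ±0.75 SD at the first randomisation and as little as ±1.46 SD in the smallest expected rerandomised comparison. These figures rest on the assumptions listed with them; the article states no SD and no confidence level. The textual finding needs none of those assumptions. Sample size, randomisation and conduct are unaffected.

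**What to change.** 1. In Conclusions, replace the efficacy sentence with a statement that the pilot will inform the design of a larger trial able to establish efficacy. The Introduction already takes this position.
2. In the Abstract's Methods, move scientific outcomes out of the list of what is primarily assessed, for example into a separate sentence that gives them as tertiary, so that the primary outcomes match Analysis, Aim 1.

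Both are wording changes. No participant, assessment or analysis is added or removed. The only cost is a more modest claim.

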## Appendix

Multimedia Appendix 1 Peer-review report by the Neilsen Foundation (USA).

## Abbreviations

AE: adverse event
IBC: individual behavioral coaching
IRB: institutional review board
M2M: movement-to-music
PAR-Q: Physical Activity Readiness Questionnaire for Everyone
REDCap: Research Electronic Data Capture
SCI: spinal cord injury
SCT: social cognitive theory
SMART: Sequential Multiple Assignment Randomized Trial
SMART-HEALTH: Sequential Multiple Assignment Randomized Trial for Home-based Exercise and Lifestyle Tele-Health
